### Work-up bias assessment

In concordance with prior NEXUS instruments, including the NEXUS C-spine, Head CT, and Chest CT rules [30, 33, 35, 46], our A/P decision tool is intended to be applied only to patients who are felt to have sufficient risk of SAPI to merit imaging. The tool is not intended for application on all patients with blunt trauma, particularly those who are determined, on the basis of clinical judgment, to have minimal risk of abdominopelvic injury and for whom A/P CT imaging is not ordered. Restricting application of the tool among low risk patients decreases the potential for generating false positive assessments, which could increase the rate of unnecessary imaging among low risk patients and markedly decrease the utility of the tool.

The success of this approach hinges on the reliability of clinical judgment, and requires that clinicians exhibit high sensitivity in their imaging decisions. High sensitivity for clinical judgment implies that clinicians will obtain imaging for virtually all injured patients, and that missed and occult injuries are rare. Therefore, an important component of our methodology is to assess the potential for unrecognized injuries among patients with blunt trauma and verify that unrecognized and occult injuries truly are rare.

Validating this approach, and verifying the high sensitivity of clinical judgment, is equivalent to assessing the potential for work-up bias, and requires a specific focus on assessing the prevalence of SAPI among patients with blunt trauma who do not undergo A/P CT imaging during their initial ED evaluation.

To conduct this assessment, we will have research assistants, present in the ED on a continuous basis, identify eligible patients during their initial visit and include them in our work-up bias study. We will complete criteria assessments for each patient at the time of presentation and follow each patient for a period of three months to determine whether at any time during this interval they returned for further care or evaluation or sought care at another facility after their discharge, whether they received any x-rays or imaging studies, and if so, what type, and whether they received any treatments, hospital admission, surgery, radiographic intervention, or died as a result of the injury.

We will classify patients as having had a missed SAPI if they underwent a surgical or interventional radiographical procedure, or died as a result of their injury during the 3- month observation period, provided they did not sustain an additional traumatic event in the interim. We expect that there will be some patients who experience multiple traumatic events (e.g., falls in the elderly) where it may be difficult to identify the exact event associated with their injuries. For the purposes of our work-up bias assessment, we will classify injuries as related to the initial traumatic event unless there is compelling information to conclude otherwise (e.g., a patient with a hip fracture who is able to ambulate between events, but becomes incapacitated after a second fall). This conservative approach is intended to overestimate, rather than underestimate, the potential work-up bias.

To form a complete data record for each patient, we will combine injury assessments with initial survey results. We will then classify each patient into one of the following three categories: 1—No missed or occult injuries; 2—Missed injury, but the patient exhibited one or more of the predictive criteria from the decision tool; or 3—Occult injury, where the patient sustained an injury but exhibited none of the decision criteria. We will report point measures and 95% confidence intervals for the prevalence of each of these outcomes among our follow-up cohort, and we will specifically use the proportion of patients with occult injuries to estimate the potential for work-up bias.

### Outcome ascertainment

As mentioned previously, we will review final radiographic interpretations to determine the presence or absence of SAPI for each patient, but will classify injuries as major, minor, or insignificant based on review of procedural records. Because we are focused on assessing the need for imaging, injuries relevant for our study must be evident on A/P CT imaging. The risk classification assigned by our instrument is immaterial if an injury is not visible on CT imaging, as the injury will not be detected by such imaging.

Because there are differing opinions on the need to diagnose all injuries versus only major clinically significant injuries, we will develop two related instruments. The first will be an instrument that is highly sensitive in detecting major injuries: a goal that will improve specificity and improve the rule’s ability to decrease imaging. The tradeoff of this approach is that the rule may miss some minor injuries, and therefore be unacceptable to some clinicians.

To accommodate this perspective, we will also develop an instrument exhibiting high sensitivity in detecting all injuries, including clinically minor injuries. This instrument will likely exhibit lower specificity and a lesser ability to decrease imaging, but will enable us to provide a decision tool that will serve all clinicians regardless of their perspectives on injury detection.

Incorporating this modification enables us to provide refined definitions for our primary and secondary objectives. The primary goal of the study is to develop a decision instrument that reliably identifies patients who harbor injuries of major clinical significance that are evident on A/P CT imaging. The secondary goal of the study will be to develop a decision instrument that reliably identifies patients who harbor injuries of major or minor significance that are evident on A/P CT imaging.

We will consider all injuries noted to be acute by the interpreting radiologists be concerning A/P injuries. Study investigators will review the medical records of any ambiguous reports and, using information from all available radiologic studies and interventional procedures, determine the final injury classification while blinded to any information about clinical variables—thus without knowledge of the patient’s classification on the basis of the decision instruments. Table 2 contains the data form we will use to collect injury information. Injury information will be concatenated with clinical data to form the final study database. While the determination of the presence or absence of SAPI will be based on the final interpretation of the imaging studies, the need for medical intervention will be based on whether the patient died as a consequence of the SAPI, or underwent an intervention related to an injury in the abdomen or pelvis during their acute care.

**Table 2 pone.0271070.t002:** NEXUS abdominal/pelvic CT imaging injury assessment form.

Patient Study Number:				
Please check one, and only one box for each row to provide your classification of the associated injury				
CLASSIFICATION^a^				
INJURY DESCRIPTION	No Injury	Clinically Insignificant Injury	Clinically Minor Injury	Clinically Major Injury

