**Major injuries**
Bladder or ureteral injury requiring intervention
Bowel injuries requiring intervention
Diaphragmatic injuries requiring intervention
Gynecological injuries requiring intervention
Hepatobiliary injuries requiring intervention
Hip fractures requiring intervention
Male genital injuries requiring intervention
Pancreatic injuries requiring intervention
Pelvic fractures (major—excludes minor avulsion injuries and non-displaced ring fractures) requiring intervention
Pelvic fractures (minor) requiring intervention
Renal injury requiring intervention
Retroperitoneal injuries requiring intervention
Spinal injuries (unstable or with neurological compromise) needing observation or intervention
Spinal injuries (stable with no neurological compromise) requiring intervention
Splenic injury requiring intervention
Vascular injury (aortic) needing observation or intervention
Vascular injury (pelvic vessels) requiring intervention
Vascular injuries (other vessels) requiring intervention

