### Data collection

Our collected data will include patient demographic information (date, time, age, sex, and race) and the presence or absence of each individual study variable. Each record will also carry embedded information indicating the identity of the institution producing the data. Because we want to increase the external validity of the study to reflect general practice, we will not provide rigid definitions for any of the individual data elements. This will help ensure that the validated low-risk criteria are widely applicable; clinicians will be asked to judge whether these elements are present on the basis of their routine clinical assessment, as they would when eventually applying the decision instruments. However, for purposes of clarification, we will provide clinicians with general descriptions of each clinical characteristic. These will be presented as informational material to all sites and will be reviewed with clinicians during in-service training sessions conducted before the beginning of the study. Potential predictor variables have been selected according to *a priori* determined associations with SAPI and acceptable inter-rater reliability [8, 17, 21, 42–45]. Additional demographic, historical, vital sign, imaging, and outcome data will also be collected (S1 File presents our data collection instrument for candidate criteria).

Our study will also collect A/P CT imaging and outcome results for each patient. All patients will have received A/P CT imaging, and may have received plain pelvic imaging. These initial studies may be supplemented by any other imaging studies deemed necessary by clinicians involved in the patient’s care.

Clinical radiologist at each site will review the x-ray and CT images and prepare final radiographic reports. We will review the final radiographic interpretations to determine whether an individual has sustained a SAPI, but will classify injuries as major, minor, or insignificant based on review of procedural records.

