### Phase 1: Derivation of optimal low-risk decision instrument(s) for A/P CT imaging

The first step in identifying suitable risk criteria is to assess the reproducibility of the assessments on the presence or absence of each individual criterion. This is achieved by having paired physicians performed independent evaluations of each criterion on patients undergoing A/P CT imaging, and comparing the results of the two assessments for each individual criterion.

For our study, each of two paired physicians will independently determine whether an individual patient exhibits any of the following potential predictor characteristics: 1) abdominal pain or tenderness, 2) flank pain or tenderness, 3) pelvic pain or tenderness, 4) hip or iliac pain or tenderness, 5) midline lumbar spine or sacral pain, 6) abdominal distention, 7) abdominal or pelvic bruising, 8) abdominal or pelvic abrasion, 9) evidence of genitourinary trauma, 10) abnormal alertness, 11) evidence of intoxication, 12) distracting painful injury, 13) hypotension, 14) tachycardia, 15) unstable vital signs, 16) low hemoglobin or hematocrit, 17) falling hemoglobin or hematocrit, 18) dangerous mechanism of injury, 19) abnormal plain radiography. For analytic purposes, each variable will be considered negative (normal) unless it can be assessed and found to be abnormal. Thus, variables that cannot be measured in an individual patient (such as pain in an unconscious individual) will be documented as “unable to assess” and treated statistically as negative. This type of imputation has the effect of ensuring that the final derivation process is based on actual observed criteria, and while this may decrease the observed sensitivity of the derivation rule (some patients may have exhibited criteria that were not assessed and been classified as not low-risk if the criteria had been assessed), it leads to a more robust derivation.

We will employ Scott’s pi statistic to assess physician inter-rater reliability of the independent assessments of each criterion and designate those exhibiting a point measure of 0.40, or greater, as exhibiting substantial inter-rater agreement and suitable for inclusion in the decision instrument. S1 File contains a copy of the survey instrument we will use to record criterion assessments.

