### Data storage and confidentiality

Temporary study index numbers will be assigned to each patient in order to link radiographic results and procedural interventions to survey data via the following procedure. At the time a radiographic request is made, the patient’s medical record number and study index number will both be recorded by a research assistant. The information in this file will be only available to the site principal investigators, and will be password protected. This file will contain no additional patient data or identifying information. The survey information for each patient will be stored in a separate secure file, and will be indexed by the assigned study numbers. This file will not contain any identifying patient information or links to individual patients. Once the radiographic and interventional results have been collected for a given patient, the study coordinators will examine the computer data file containing patient medical record numbers and ascertain the corresponding study index number. Radiography reports and outcomes will then be copied and labeled with the study index number, effectively redacting all identifying information from the report. The relabeled photocopies and outcomes will then be forwarded to a central repository for concatenation with the study survey data. At the completion of the study, the data linking each patient’s medical record and study index number will be deleted from each site’s encrypted database.

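### Blinding is overstated for ambiguous cases: the investigators who grade them read the medical record, where the findings behind the rule's criteria would be recorded, and no masking step is described

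*Protocol article*

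**What the plan says.** Two routes lead to an injury grade in the protocol article. In the routine one (Data collection; Outcome ascertainment), the final radiology report settles whether an injury is present, and the investigators "will classify injuries as major, minor, or insignificant based on review of procedural records". The second is for unclear cases: "Study investigators will review the medical records of any ambiguous reports". How the grading is then done in these cases is described in the following terms: "using information from all available radiologic studies and interventional procedures, determine the final injury classification while blinded to any information about clinical variables". The same sentence goes on to infer from this that the reviewers do not know how the decision instruments classify the patient.

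Three other places bear on this:

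- **Human subjects considerations and procedures:** the study data come from the routine examination and evaluation.
- **General design; Core methods; Validation of the A/P CT decision instruments:** the rule is positive if any one criterion is present.
- **Data storage and confidentiality:** the survey is kept in a separate file. For the outcome material, "Radiography reports and outcomes will then be copied and labeled with the study index number", a step described as redacting identifying information.

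**The concern.** The blinding statement and the instruction to open the medical record conflict as worded. An emergency department note would normally hold pain and tenderness, alertness, intoxication, distracting injury and blood pressure. A reader of that note can largely infer whether the rule was positive without seeing the survey. The article rests blinding to the rule classification on blinding to the variables, so if the second is not secured, neither is the first.

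The likely direction is favourable to the rule. A reviewer who sees an alert, sober patient without tenderness may settle an equivocal CT finding as insignificant or as no injury. In a rule-negative patient that removes a false negative and raises the sensitivity and negative predictive value on which validation depends. The study would also report blinded adjudication that its described procedure does not support.

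**Working it through.** **1. What the reviewer would see.** Preliminary work (inter-rater Results) lists nine criteria that passed the reliability screen: five pain or tenderness items, abnormal alertness, intoxication, distracting painful injury and hypotension. All nine are findings of a routine examination. Data storage and confidentiality separates the survey and removes identifiers. Nothing there removes history, examination or vital signs from the records reviewed.

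**2. Where judgement can move a grade.** In Table 1 nearly every major category requires an intervention, and Outcome ascertainment ties need for intervention to a procedure performed or to death from the injury. These are mostly recorded events. Judgement remains in:

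- minor versus insignificant, which turns on whether observation was needed, and minor versus no injury (secondary instrument);
- whether an intervention, or a death, was related to the abdominal or pelvic injury, for example blood products or pressors in a multiply injured patient;
- aortic injuries and "Spinal injuries (unstable or with neurological compromise) needing observation or intervention", which can be major without an intervention.

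**3. Planned numbers.** Sample size calculations gives 317 major injuries per phase. At 5% prevalence, 317 / 0.05 = 6,340 patients, which reproduces. The 317 itself does not follow from the stated inputs: with X = N, tail 0.025 and P_L = 0.98, the article's formula gives N = 183. That is a separate matter. Here 317 is simply the planned number of injuries.

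**4. Effect of one downgrade on the primary instrument.** Validation requires the lower 95% limit to exceed 98%. The article's formula is P_L = X / [X + (N − X + 1)·F], with F the upper 0.025 point on 2(N − X + 1) and 2X degrees of freedom.

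| Detected / major injuries | F | Lower limit | Verdict on sensitivity |
|---|---|---|---|
| 317/317 | 3.710 | 317/(317 + 3.710) = 98.84% | pass |
| 316/317 | 2.806 | 316/(316 + 2 × 2.806) = 98.26% | pass |
| 315/317 | 2.428 | 315/(315 + 3 × 2.428) = 97.74% | fail |
| 315/316 | 2.806 | 315/(315 + 2 × 2.806) = 98.25% | pass |

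The last row is the relevant comparison. A missed major injury that is downgraded leaves the denominator; it does not become a detection. Going from 315/317 to 315/316 turns a fail into a pass. With 3 misses, one downgrade gives 314/316 (97.73%), still a fail. With 0 or 1 miss the rule passes anyway. So one downgrade matters only at exactly 2 misses.

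**5. How often that boundary is met.** P(exactly 2 misses) = C(317, 2)·q²·(1 − q)^315, with q = 1 − sensitivity. The true sensitivity is an assumption, shown as a range.

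| Assumed sensitivity | P(exactly 2 misses) |
|---|---|
| 99.9% | 3.7% |
| 99.8% | 10.7% |
| 99.5% | 25.8% |
| 99.0% | 21.1% |

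These are probabilities of standing at the boundary. A flip also needs one of the two misses to be an ambiguous case that is graded down.

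**6. Negative predictive value.** About 10% of patients are free of all criteria, so 0.10 × 6,340 = 634. Five misses give a lower limit of 98.17% (pass) and six give 97.95% (fail). Sensitivity is the tighter test.

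**7. How many cases are exposed.** The article gives no number of ambiguous reports. If 1% to 5% of 6,340 scans were ambiguous (assumption), that is 63 to 317. Only rule-negative cases could have a miss removed: at 10%, about 6 to 32. Fewer still could be graded down from major.

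**The case against.** The strongest defence reads the term clinical variables as the items forming the rule, the sense used in the validation section, and notes that the sentence bases classification on radiology and interventions, not on the emergency department examination. The survey sits in a separate file and is joined to the outcomes afterwards, so blinding to the survey and to the computed rule status is workable. Masking of charts may be described in the full protocol, which is not shown. Severity mostly follows recorded events.

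Much of this stands, and it rules out several stronger readings that a reader might infer:

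- **That there is no blinding at all.** Not supported: blinding to the survey and the formal classification can be carried out as described.
- **That grading is impossible under blinding because it needs neurological compromise.** Not supported: that is not one of the 19 candidate criteria.
- **That reading all radiology unblinds the rule.** Abnormal plain radiography is a candidate ("18) dangerous mechanism of injury, 19) abnormal plain radiography"), and patients may have had pelvic films. But the preliminary conclusions report only moderate to poor agreement for all other criteria, so it would probably not enter the rule.
- **That primary validation as a whole is at risk.** Most major grades depend on an intervention or death, and the flip occurs only at one boundary.

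What the defence does not remove is the instruction to review the medical records. Narrowing the term to the rule's items does not help, because those items are what the record would contain. The article makes a positive claim of blinding that its own described procedure does not secure.

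**Conclusion.** The point holds in limited form. For ambiguous cases the stated blinding goes further than the described procedure can deliver. The likely bias favours the rule and falls mainly on the minor versus insignificant or no-injury grading of the secondary instrument. Its size there cannot be given, because the article states neither the number of ambiguous reports nor the expected number of minor injuries. For the primary instrument the exposure is narrow: a single downgrade changes the sensitivity verdict only at exactly 2 misses, with probability about 4% to 26% over the assumed sensitivities. This rests on 317 major injuries being observed, on the article's exact two-sided limit, and on the full protocol not already specifying masked records. It should be corrected because the change is cheap and the blinding will be reported as a design strength.

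**What to change.** - Have coordinators give reviewers an index-numbered extract holding the CT and other radiology reports and the intervention, procedure and outcome records, with emergency department history, examination and vital signs withheld.
- State that no reviewer grades a patient whose criteria survey they completed.
- Apply both rules to every injury grading, not only to ambiguous reports.
- Acknowledge that transfusion or pressor records may still hint at hypotension. Where masking is not possible, limit the claim to blinding to the criteria survey and the computed rule status.

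The cost is a change of wording and a somewhat longer extract, since coordinators already copy and relabel reports and outcomes. The small downside is that reviewers will have less context in a few equivocal cases.

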## Materials and methods

### Defining primary outcomes via expert panel review

Previous experience has shown that clinicians differ in their tolerance for missing minor injuries and in their definitions as to what constitutes a clinically significant injury. Many clinicians are comfortable using tools that occasionally miss injuries that require no intervention, provided all major injuries are identified. Other clinicians seek to identify all injuries regardless of their clinical significance [38].

To accommodate varied perspectives on clinically significant injury, we employed a modified Delphi process and convened an expert panel consisting of three trauma surgeons, three emergency medicine physicians and radiologist to define the following study outcome classifications of injuries seen on CT: clinically significant major injury, minor injury, and insignificant injury.

Our final outcome classification scheme is based in results of this Delphi process among this expert panel. Under this schema, injuries of major clinical significance consist of all abdominal and pelvic injuries requiring intervention, as well as any injury to the aorta, and any injury to the spine associated with instability or neurological compromise. Injuries that require only observation, but no intervention, will be considered clinically minor, provided they do not involve the aorta or spine, while injuries that required neither intervention nor observation will be considered insignificant. See Table 1.

**Table 1 pone.0271070.t001:** Classification of injuries based on Delphi consensus.

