We will assign a final clinical outcome for each patient based on the results of A/P CT imaging as well as the patient’s hospital course. Patients who we designate as having injuries must have injuries evident on CT imaging. This reflects the fact that if injuries are not apparent on CT imaging, it is immaterial whether the patient underwent such imaging. Furthermore, we will classify each patient as having, in order of increasing severity: 1—no injuries (no injuries evident on CT); 2—insignificant injuries (e.g., minor bruising, small hematomas, or isolated small avulsion fractures); 3—clinically minor injuries (significant injuries that require no specific intervention); and 4—clinically major injuries (significant injuries that require specific intervention or result in patient death). Our final outcome classification will be based on the most severe type of injury sustained by each patient. We will concatenate our final outcome assignments with the criterion assessments to create our final analysis database.

We will apply chi-squared binary recursive partitioning to this data set to identify separate combinations of criteria that identify both major and minor significant abdominopelvic injuries with > 98% sensitivity and > 98% NPV, assuming such combinations exist. If more than one combination of variables exhibits the requisite sensitivity and negative predictive values for injury, the combination with the highest specificity will be adopted as the optimal low-risk decision instruments.

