### Global assessment of potential missed injuries

For patients enrolled in the study and admitted as inpatients, hospital discharge summaries will be reviewed in order to determine whether any SAPI were missed by the initial ED evaluation. We will also review trauma, surgery and mortality logs, and quality improvement records to identify any cases of SAPI that were missed on initial presentation (including patients enrolled in the work-up bias assessment), and whether the involved patients underwent A/P CT imaging.

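### Need for intervention in imaged patients is read only during an undefined acute-care period, so a CT-visible injury first treated later drops out of the primary sensitivity

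*Protocol article*

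**What the plan says.** The primary goal, under Outcome ascertainment, is an instrument that "reliably identifies patients who harbor injuries of major clinical significance that are evident on A/P CT imaging". For most injuries, Table 1 separates major from minor by whether the injury requires intervention, and sets no time limit. The section on the expert panel adds: "Injuries that require only observation, but no intervention, will be considered clinically minor, provided they do not involve the aorta or spine". Injuries needing neither intervention nor observation are insignificant.

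Two places say how this is read in imaged patients. The Phase 1 section assigns the outcome "based on the results of A/P CT imaging as well as the patient’s hospital course" and counts an injury that results in death as major, without a time limit. Outcome ascertainment takes intervention to have been needed by those who "died as a consequence of the SAPI, or underwent an intervention related to an injury in the abdomen or pelvis during their acute care". Neither defines acute care, and no follow-up after discharge is stated for imaged patients. The Phase 2 section keeps the same outcome assessment for validation.

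Patients without CT are handled separately under Work-up bias assessment. The plan is to "follow each patient for a period of three months to determine whether at any time during this interval they returned for further care", and a missed injury is one leading to a surgical or interventional radiology procedure, or a patient who "died as a result of their injury during the 3- month observation period".

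Global assessment of potential missed injuries is the one place that looks further: "For patients enrolled in the study and admitted as inpatients, hospital discharge summaries will be reviewed", together with trauma, surgery and mortality logs and quality improvement records. Its stated purpose is to find injuries missed at the initial evaluation.

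**The concern.** Whether an injury requires intervention is a property of the injury. Whether an intervention took place in acute care is a narrower observation, and the primary outcome rests on the narrower one. Consider a splenic, bowel or stable spinal injury that is reported on the index CT, observed, sent home and operated on later. It was visible on CT and it did require intervention, yet it is graded minor. The plan's argument that an injury invisible on CT is irrelevant to an imaging rule does not apply to it.

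If that patient met none of the criteria, a false negative of the major-injury instrument is counted as a true negative. Among rule-negative patients the error can only favour the rule. Because both phases use the same outcome, it affects the derivation as well as the validation. What is at stake is the claim that the rule has been validated for major injury.

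**Working it through.** **1. What happens to an injury first treated after acute care (Table 1)**

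| Injury seen on index CT, no intervention in acute care | Grade | Primary outcome | Secondary outcome (major or minor) |
|---|---|---|---|
| Aortic, or unstable or neurologically compromised spinal, needing observation | Major | counted | counted |
| Other injuries, observed | Minor | lost | counted |
| Diaphragmatic injury or major pelvic fracture, not observed | Minor | lost | counted |
| Most other injuries, not observed | Insignificant | lost | lost |

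The footnote to Table 2 counts blood products, anticoagulation reversal and pressors as interventions. The affected patients are therefore those who had none of these, and no procedure, during acute care.

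**2. Does the log search recover them?** It looks for injuries missed at presentation. An injury reported on the index CT was not missed, and nothing says that its grade is revisited.

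**3. The plan's own figure.** Inputs from the sample size section: two-sided alpha 0.05, exact limit P_L = X / [X + (N − X + 1)·F], with F the upper 2.5% point on 2(N − X + 1) and 2X degrees of freedom, and X = N. The stated N for a 98% limit is 317. The formula with no misses gives N = 183 (98.00%; N = 182 gives 97.99%). So 317 does not reproduce. It is larger than needed, which is a separate matter. The chain 317/0.05 = 6,340 does reproduce.

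**4. Misses tolerated at N = 317.** The validation section requires lower limits above 98%.

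- 0 misses: 317/(317 + 1 × 3.7104) = 98.84%
- 1 miss: 316/(316 + 2 × 2.8061) = 98.26%
- 2 misses: 315/(315 + 3 × 2.4283) = 97.74%

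The same formula needs at least 277 major injuries to allow one miss and 359 to allow two.

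**5. Adding late-treated injuries back.** Start from 317 acute-care major injuries, all detected, and add d late-treated injuries in rule-negative patients. The values of d are assumed, because the documents give no rate.

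| d | Sensitivity | Lower limit |
|---|---|---|
| 1 | 317/318 = 99.69% | 98.26% |
| 2 | 317/319 = 99.37% | 97.75% |
| 3 | 317/320 = 99.06% | 97.28% |
| 5 | 317/322 = 98.45% | 96.41% |

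If one miss is already counted among the 317, a single added case gives 316/318 and a lower limit of 97.75%.

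Rule-positive late cases add no misses and raise the limit slightly. With 10 late cases, 2 of them rule-negative, it is 97.81%; with 17, 2 of them rule-negative, 97.85%. Two misses pass only from 359 major injuries, which means 359 − 317 = 42 late cases with 40 of them rule-positive.

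**6. NPV.** The sample size section puts about 10% of patients free of the criteria: 0.10 × 6,340 = 634. The exact lower limit is 98.87% with 2 misses, 98.17% with 5 and 97.95% with 6.

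**The case against.** The strongest objection is that the two follow-up periods do different jobs. Un-imaged patients have no CT, so three months of follow-up is their reference standard for whether an injury existed. In imaged patients CT settles that, and intervention only grades severity. The cohorts are never pooled. This stands: a reader might infer that acute care for one cohort and three months for the other is an internal contradiction, or that three months is the plan's general standard for late harm. The documents support neither. The point rests on Table 1 against Outcome ascertainment, within the imaged cohort.

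Second, acute care is undefined, so an emergency readmission might fall within it, and a full protocol may define the term. That also stands, and it limits how firmly one can say who is lost. The article does, however, state an outcome definition here, and as stated it can be read in more than one way.

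Third, an observed injury graded minor still counts in the secondary rule, which faces the same 98% criterion. True, but the primary rule makes its own claim, and most injuries neither treated nor observed leave both outcomes.

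Fourth, a reader might infer that late interventions cluster in patients who first looked well, and so in rule-negative patients. Nothing in the documents says so. Without that premise the size of the bias is unknown, and the two-patient case illustrates fragility without estimating it.

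**Conclusion.** The concern holds in a limited form. The primary outcome counts interventions only within an undefined period, although Table 1 sets no time limit, and no later step regrades a CT-visible injury treated afterwards. The direction is clear for rule-negative patients: sensitivity is overstated.

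The size cannot be derived from the documents and may be small. What can be shown is how little it takes. At 317 major injuries and no other misses, two rule-negative late-treated patients change a pass into a fail; if one miss is already counted, one is enough. This assumes that the validation phase yields about 317 major injuries and that few rule-positive late cases are added back with them.

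A reader might infer that NPV is equally exposed. It is not: on the plan's 10% figure it would take six misses.

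**What to change.** 1. Under Outcome ascertainment, define the acute-care window, including whether a readmission for the same injury falls within it, and give death from the injury a window.
2. When the trauma, surgery, mortality and quality records are searched under Global assessment of potential missed injuries, also record any intervention for, or death from, an injury already seen on the index CT within a fixed period. The three months used for un-imaged patients is one possible choice.
3. Report sensitivity and NPV with these injuries regraded as major, alongside the acute-care-only result. If the two fall on different sides of the 98% criterion, limit the validation claim to interventions in acute care.

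The cost is protocol wording and a later outcome lock, by about three months if that period is chosen. The search must be finished before the file linking record and study numbers is deleted at study completion. Care at other hospitals will still be missed, since the logs do not replace patient follow-up. Some non-urgent later procedures will be counted, and sensitivity may come out slightly lower.
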